## Aim

The aim of the trial was to investigate if intraoperative intraperitoneal administration of fosfomycin, metronidazole and recombinant human granulocyte-macrophage colony stimulating factor followed by oral antibiotic for three days (intervention group) was as effective as the current intravenous antibiotic treatment given during and three days (control group) after appendectomy for perforated appendicitis. We evaluated this through length of stay.

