## Outcomes

### Primary outcome

Total length of in hospital stay (measured in hours) was defined as from end of the surgery until discharge from the hospital plus length of stay during a possible readmission within 30 days from surgery. The latter was calculated based on a review of the patient's record 30 days postoperatively ( $\pm 3$  days).

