#### **Sample size**

The power calculation for the trial was as follows. The cumulative 30-day length of stay was expected to be 72 hours with a standard deviation of 12 hours in the control group. When  $\alpha$  was set at 0.05,  $\beta$  was set at 0.80, and an acceptable difference between the groups was set at 48 hours, a randomised design requires 4 patients in each group, a total of 8 patients. However, as we expected data not to be normally distributed and planned to use a quasi-randomised design [8,9], we decided to include 6 patients in each group, a total of 12 patients to ensure sufficient power.

A participant has concluded the trial when the 30-day postoperative follow-up has been conducted. Inclusion of participants in the trial will continue until a minimum of six participants in each study group have reached the 30-day follow-up with data for the primary outcome parameter, total length of stay. Thus, we planned to include six patients in each study group and only if the primary outcome was not available at 30-day follow-up, further patients were included to ensure data on the primary outcome on six patients in each group.

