### Secondary endpoints

We expect that the data are not normally distributed due to the low number of participants. No statistical test will be used to compare the secondary endpoints in the two groups due to the lack of power. The results will therefore be descriptively presented.

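### The SAP judges whether the new regimen is as effective by total length of stay alone, a measure in which short readmissions and failures treated without readmission can go unseen

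*SAP*

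**What the plan says.** The Aim section asks whether the new regimen "was as effective as the current intravenous antibiotic treatment given during and three days (control group) after appendectomy for perforated appendicitis". The intervention arm takes its three postoperative days of antibiotic orally. The section then names one measure for the question: "We evaluated this through length of stay".

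The primary outcome is time in hospital "from end of the surgery until discharge from the hospital plus length of stay during a possible readmission within 30 days from surgery", that is, one sum of index and readmission hours. The Sample size section states: "The cumulative 30-day length of stay was expected to be 72 hours with a standard deviation of 12 hours in the control group". It adds that "an acceptable difference between the groups was set at 48 hours", without saying in which direction or whether this is an effect to detect or a margin to tolerate. The Primary endpoint section plans a Mann-Whitney U-test.

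Deep surgical site infection, intraabdominal abscess, readmission and reoperation are secondary. They are tabulated as number and per cent by arm (SAP, Complications, Table 3), and for all secondary endpoints "No statistical test will be used to compare the secondary endpoints in the two groups due to the lack of power". No interval is planned for them.

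**The concern.** Effectiveness here means control of infection after perforated appendicitis. Hours in hospital depend on that, but also on how the drug is given. The control course is three days intravenous and the expected control stay is 72 h = 3 × 24 h, while the intervention is oral. If control patients stay for their intravenous course, the arms would differ in stay even with identical infection control.

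Summing the hours adds a second problem. An intervention patient discharged at 24 h and readmitted for 40 h totals 64 h, and ranks better than an uncomplicated control at 72 h. A failure treated without readmission adds no hours after discharge.

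The Aim links the effectiveness question to nothing except this total. A shorter stay could therefore be reported as support for effectiveness while more intervention patients had failed. Changing the test or the margin would not help, because the difficulty lies in what the outcome measures.

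**Working it through.** **The plan's own figure.** Inputs from the Sample size section: difference 48 h, SD 12 h, α 0.05 (two-sided assumed), power read as 0.80. A two-sample t-test has power 56.5% with 2 per group, 94.8% with 3 and 99.6% with 4, so it needs 3. For an exact Mann-Whitney test the smallest two-sided p is 2/20 = 0.10 at 3 v 3 and 2/70 = 0.029 at 4 v 4. The stated 4 per group is thus the smallest workable number for the planned test, and it reproduces.

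**Rejection rule at 6 v 6.** There are 924 equally likely orderings under the null. U ≤ 5 covers 19 of them: p = 2 × 19/924 = 0.041. U ≤ 6 covers 30: p = 2 × 30/924 = 0.065. The test is significant when U ≤ 5.

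**Break-even.** A readmitted intervention patient equals the average control when readmission hours = 72 − index stay. That is 48 h for a 24 h index stay, 36 h for 36 h, and 24 h for 48 h. Shorter readmissions still rank as better than the average control.

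**Simulation.** Control stay is normal, mean 72 h, SD 12 h (Sample size section). Assumptions not in the SAP: intervention index stay of 24 h (72 − 48), 36 h or 48 h with the same SD; 2 of 6 intervention patients readmitted; no control failures. The table gives the share of trials with a significantly shorter intervention stay:

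| Index stay | No added hours | 24 h readmission | 36 h | 48 h | 72 h |
|---|---|---|---|---|---|
| 24 h | 100% | 98% | 83% | 42% | 0.4% |
| 36 h | 99% | 79% | 39% | 8% | 0% |
| 48 h | 83% | 29% | 6% | 0.4% | 0% |

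The column with no added hours also applies when patients fail after discharge and are treated without readmission, however many there are.

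With 1 of 6 readmitted at a 24 h index stay, the shares are 99.6% for 24 h, 85% for 48 h, 26% for 72 h and 0% for 120 h. One patient above all six controls, with the other five below them, gives U = 6 and p = 0.065. Two such patients give U = 12 and p = 0.39.

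**Allowing control failures.** Take failure risks of 30% (intervention) and 10% (control), and a 24 h index stay. With 48 h readmissions, 62% of trials show a significantly shorter intervention stay, and 33% show this together with more failures in the intervention arm. With 96 h readmissions the figures are 26% and 0.1%.

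**What the failure outcomes can show.** For 0 failures in 6 the exact 95% upper limit is 1 − 0.025^(1/6) = 0.459, or 46%. Fisher's exact p is 0.45 for 2 of 6 against 0 of 6, and 0.061 for 4 of 6 against 0 of 6.

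**The case against.** Four stronger readings are tempting, and the SAP does not support them.

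- *The control stay is fixed by the intravenous course.* A reader might infer this from 72 h and three days. The SAP gives no discharge criteria and no rule tying discharge to the end of treatment. Such rules may stand in the protocol, which is not at hand. An SD of 12 h also fits discharge on recovery.
- *A large reduction in stay is what equal effectiveness would produce.* This needs an expected intervention stay, and none is given. The 48 h is called acceptable and has no direction, so it can be read as a tolerated margin, in which case no reduction is expected.
- *Failures are ignored.* They are defined, collected to day 30 and tabulated by arm. Lack of power is a sound reason for not testing them, as the Fisher values show. Adding readmission hours is also a real safeguard: with two failures and a 24 h index stay, significance is all but gone at 72 h.
- *The plan will declare a worse regimen effective.* The SAP has no explicit rule that a shorter stay means equal effectiveness.

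What remains is that the Aim ties effectiveness to stay and to nothing else, that the safeguard does not reach short readmissions or failures treated without readmission, and that nothing says how the tabulated failures bear on the conclusion. Discharge criteria in the protocol would not turn hours in hospital into a measure of infection control.

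**Conclusion.** The point holds in a limited form. Total stay measures hospital use and cannot by itself support a statement that the regimens are equally effective. How much failure it can hide depends on values that the SAP does not give. With 2 of 6 intervention patients readmitted and no control failures, the chance of a significantly shorter stay runs from 98% (24 h index stay, 24 h readmission) to practically nil (72 h readmission at any index stay examined). The masking needs a short index stay together with short readmissions, or failures treated without readmission. The tabulated failures cannot fill the gap unless their uncertainty is shown, since no failures in six patients is compatible with a true risk of up to 46%. This should be fixed, mainly in what the report claims. It does not make the length-of-stay comparison itself invalid.

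**What to change.** 1. Reword the aim and the planned conclusion: total length of stay measures hospital use under the two regimens, and a shorter stay is not by itself evidence of equal effectiveness.
2. Beside the total, report index stay and readmission hours separately by arm.
3. For deep infection, abscess, readmission, reoperation, and patients with any of these, give the number per arm and the risk difference with an exact 95% confidence interval. State that six per arm cannot exclude a large excess of failures.
4. Before doing so, reconcile the abscess definition. The Intraabdominal abscesses section excludes collections that were not drained, while the organ/space criteria in Table 5, to which it refers, can be met without drainage. One definition should apply throughout.
5. The SAP describes much of its data collection in the past tense. If the combined outcome is added after data were seen, label it post hoc.

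The cost is wording and one small table, from data already collected. The price is a more modest claim with very wide intervals.

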## Design

Non-blinded, Q-RCT with a minimum of 6 participants in each group: intervention and control – a total of minimum 12 participants. The control and intervention group were included at two different hospitals.

We chose a quasi-randomized design to make the trial feasible within a manageable timeframe. The trial only included patients with appendix perforation. A rather large number of patients undergo surgery for suspected appendicitis, however, only around 75% of these patients are diagnosed with appendicitis at surgery [1]. Of these, only around 30% are diagnosed with complicated appendicitis at surgery [2]. So even if all possible patients were enrolled, only around 10-20% of the patients could be included in the trial. We anticipated that the feasibility of the trial would be increased with the design as a Q-RCT for three reasons. One, if each centre only had to implement one regimen for the seldom trial participant, it would be easier to ensure that this regimen could be applied day and night. Two, if the two groups of patients were included in parallel, the period of inclusion would be shorter because of the double catchment area for patient accrual. Three, the control group could be more efficiently included as only patients, where perforated appendicitis was found during laparoscopic appendectomy were approached and asked to participate.

We are convinced that the populations at Herlev Hospital and Bispebjerg Hospital, which are both located in the Copenhagen area, are comparable, so that the possible risk of bias was minimized. Both departments use the same surgical therapy for perforated appendicitis.

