## Endpoints

### Primary endpoint

The difference in total length of stay measured in hours will be compared between the intervention and the control group. Total length of stay was defined as from end of the operation until discharge from the hospital plus length of stay during a possible readmission

within 30 days from surgery. All randomised participants will be included in the analysis (intention-to-treat) if all data have been collected for 30 days postoperatively). The length of stay will be presented as a continuous numerical variable in the Result section of the manuscript. We expect that the data are not normally distributed due to the low number of participants, thus, medians and range for the intervention and control group will be presented. Furthermore, a Mann-Whitney U-test will be performed to compare the length of stay between the two groups.

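### With one hospital per arm, treatment and hospital cannot be separated, yet the SAP labels the primary analysis as randomised and intention-to-treat and says bias was minimised

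*SAP*

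**What the plan says.** **SAP, Design.** The trial is described as "Non-blinded, Q-RCT with a minimum of 6 participants in each group: intervention and control". On allocation: "The control and intervention group were included at two different hospitals". One of three feasibility reasons is that it would be easier "if each centre only had to implement one regimen for the seldom trial participant". Comparability is asserted: "We are convinced that the populations at Herlev Hospital and Bispebjerg Hospital, which are both located in the Copenhagen area, are comparable". The section draws its conclusion about bias from that conviction: "so that the possible risk of bias was minimized". It adds that both departments use the same surgical therapy.

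**SAP, Sample size.** A randomised design is said to need 4 per group (control mean 72 h, SD 12 h, difference 48 h). Because non-normal data were expected and the authors "planned to use a quasi-randomised design [8,9], we decided to include 6 patients in each group". The two references are notes on cluster randomisation. No intracluster correlation (ICC) or design effect is given.

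**SAP, Baseline characteristics.** The quasi-randomised design is acknowledged as a possible source of group differences, and baseline p-values are planned for that reason.

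**SAP, Primary endpoint and Statistical methods.** "All randomised participants will be included in the analysis (intention-to-treat"), subject to complete 30-day data. Length of stay is compared by a Mann-Whitney test, with p ≤ 0.05 as the threshold. Nothing limits the result to a contrast between hospitals.

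**The concern.** If each hospital gives one regimen, then knowing the hospital is knowing the treatment. Any difference in stay is the sum of a treatment effect and a hospital effect, and the data cannot apportion it. A patient-level test treats the 12 patients as if they had been allocated independently, so its nominal error rate applies to the statement that the two hospital groups have the same distribution of stay. It does not apply to the statement that the two treatments do.

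The primary outcome ends at discharge, which is a decision made by staff in an open trial. Local discharge practice is a plausible source of a hospital difference, though the SAP documents nothing about it either way.

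At stake is the meaning of the primary result. Called randomised and intention-to-treat, a significant difference would be read as caused by treatment, and a small one as support for the aim of showing the new regimen as effective. A hospital difference can produce either.

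**Working it through.** **1. What can be estimated.** Write stay = μ + τT + ηH + error, where T is treatment and H is hospital. One regimen per centre makes T = H for every patient, so only τ + η can be estimated. With one hospital per arm there are 1 − 1 = 0 degrees of freedom between hospitals within each arm. A hospital term cannot be fitted, and more patients at the same two hospitals do not change this.

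**2. The SAP's own sample size.** Inputs: 48 h difference, SD 12 h, α 0.05 (taken as two-sided), 80% power.
- The noncentral-t calculation gives power 56.5% at 2 per group and 94.8% at 3, so 3 suffice.
- The smallest attainable two-sided Mann-Whitney p is 2/C(2n, n): 2/20 = 0.100 at n = 3 and 2/70 = 0.029 at n = 4. Four is the first size at which the planned test can reach significance, with simulated power of 97%.
- At 6 per group, simulated power exceeds 99.9%.

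The stated 4 is consistent with this, and 6 is ample for power on the SAP's inputs.

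**3. What the rise from 4 to 6 can do.** Read as a cluster inflation, it is a design effect of 6/4 = 1.5. Solving 1 + (6 − 1) × ICC = 1.5 gives ICC = 0.10. Such an inflation presupposes several clusters per arm. With one per arm, the hospital part of the difference has SD 12 × √(2 × ICC), with 12 h taken as the total SD. At ICC 0.10 that is 12 × √0.20 = 5.4 h, however many patients are enrolled.

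**4. Size, with no treatment effect.** Normal stay, SD 12 h, exact Mann-Whitney. At 6 v 6, reject if U ≤ 5 or U ≥ 31 (38/924 = 4.1% exact size). At 4 v 4, reject if U = 0 or 16 (2/70 = 2.9%). The hospital differences and ICCs are assumptions, since the SAP gives none.

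| Assumed hospital difference | p ≤ 0.05 at 6 v 6 | p ≤ 0.05 at 4 v 4 |
|---|---|---|
| 0 h | 4% | 3% |
| 6 h | 10% | 6% |
| 12 h | 30% | 14% |
| 18 h | 59% | 29% |
| 24 h | 83% | 49% |

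With random hospital effects instead, ICC 0.05, 0.10 and 0.20 give about 7%, 10% and 16% at 6 v 6. For a given hospital difference, the larger sample detects it more often, so raising n does not protect the treatment claim. A small part of the increase from 4 to 6 comes from the larger exact size of the test.

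**5. The other planned safeguard.** Baseline tests at 6 v 6 have little power, and the listed variables (age, sex, body size, ASA score, preoperative antimicrobials, length of surgery) do not capture discharge practice. The primary comparison is not adjusted for any of them.

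**The case against.** The strongest reply is that this is a disclosed choice. The Design section states the two-hospital allocation, calls it quasi-randomised and gives three feasibility reasons. Sample size and Baseline characteristics repeat the term, and the latter concedes that groups could differ. Inclusion is reported in the past tense, so no edit can remove the confounding. All of this stands. It limits the point to labels and interpretation, without answering it, because the Primary endpoint section drops the qualification and Design still says bias was minimised.

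Some stronger readings are tempting but not supported:

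- *That nothing was randomised.* The SAP does not say how each hospital received its regimen. What follows is only that no individual could be randomised between regimens. A coin toss between the hospitals would still leave one cluster per arm.
- *That the claim of sufficient power is false.* It is not, on the SAP's inputs, and non-normality is a separate stated reason for 6 per group. The problem is bias, not power.
- *That discharge followed ward routine.* The SAP does not say so. A three-day control regimen and an expected 72 h stay suggest, without proving, that the regimen itself also influences discharge.
- *That the arms were recruited differently.* The SAP says "the control group could be more efficiently included as only patients, where perforated appendicitis was found during laparoscopic appendectomy were approached", but does not describe how intervention patients were approached. A difference is an inference.

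**Conclusion.** The point holds for interpretation and labelling. The confounding follows directly from the Design section and needs no assumed figures. The primary p-value compares two hospital groups and is not by itself a test of treatment, and the planned remedies do not change that. Calling the participants randomised and the analysis intention-to-treat, and saying that the risk of bias was minimised, claims more than the design supports.

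The percentages are illustrations under assumed hospital differences or ICCs, normal data and an SD of 12 h. A reader might take 83% as this trial's error rate. It is not: 24 h is two within-hospital SDs, and the SAP gives nothing from which to judge whether the true difference is near that or near zero. Nor does the point show that the hospitals differed. It shows that the trial cannot tell.

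**What to change.** 1. **Primary endpoint:** replace the wording on randomised participants and intention-to-treat by *all enrolled participants, by hospital/regimen*.
2. **Design:** describe the trial as *a non-randomised parallel comparison of two hospitals*. The feasibility reasons can stay.
3. **Design:** replace the claim that bias was minimised by a statement that comparability of the hospitals is assumed and that hospital and treatment are fully confounded.
4. **Primary endpoint:** add that the Mann-Whitney p-value compares the two hospital groups and is not by itself a test of treatment.

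Optional: report the shift in hours, applied to one arm, that would move the Mann-Whitney result across p = 0.05. The SAP plans no interval and no decision rule at 48 h, so this would be an added sensitivity line tied to the p-value. If records allow, show pre-trial stay for perforated appendicitis at both hospitals as a reference for that shift.

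The sample-size statement on power needs no change for this point. The cost is a few sentences in the SAP and manuscript, plus one short calculation and some record work if the optional items are taken up. The downside is a more modest claim.

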## Outcomes

### Primary outcome

Total length of in hospital stay (measured in hours) was defined as from end of the surgery until discharge from the hospital plus length of stay during a possible readmission within 30 days from surgery. The latter was calculated based on a review of the patient's record 30 days postoperatively ( $\pm 3$  days).

### Secondary outcomes

#### *Questionnaires*

##### Gastrointestinal Quality of Life Index (GIQLI)

A disease-specific questionnaire [3] validated in Danish [4] was collected at 10 days postoperatively ( $\pm 2$  day) and at 30 days postoperatively ( $\pm 3$  days). The questionnaire evaluates the quality of life after surgery. It contains 36 questions, which explores five main domains: symptoms (19 items), physical status (seven items), emotions (five items), social functioning (four items), and the effect of medical treatment (one item). A five-point Likert-scale (0–4 points) is used to answer all items. The scale ranges from “never” to “all the time”. A higher score denotes a better function.

##### Harms

A questionnaire regarding harms was filled out by the patients, see Supplements, Table 2. Questions about side effects was evaluated at the first, postoperative day and 10 days ( $\pm 2$  days) postoperatively when the patients had their sutures removed by the trial personnel. The questionnaire evaluates the possible harms of the trial treatment and was based on the answers of participants in of previous trial [5]. It contains seven questions, where the participant can describe if a possible harm has arisen. The scale has five possible answers, which ranges from “never” to “all the time”. The final, eighth questions, gives the participant a possibility to describe any change they have experienced after the surgery.

